#### Confidentiality

Study staff will be trained on the protection of patient confidentiality. Prior to the study, study site coordinators will meet with clinic staff and peer counselors to identify additional strategies appropriate to the local setting to improve participant confidentiality. Access to electronic data will be restricted to research staff directly involved in implementation and evaluation of the pilot. All electronic data will be de-identified and recorded through use of an identification number for each HIV-positive woman and her HIV-exposed infant. The link between participant name and identification number is known only by the site coordinator who conducts enrollment and by the provider who has an established care relationship with the participant. The record linking patient name and electronic ID will be securely stored in a locked office. De-identified data will be used for all analyses and results will be reported as aggregates and ratios.

#### Study outcomes

##### Acceptability and uptake

Key informant interviews will document attitudes, preferences, perceived benefits, and concerns from the perspective of stakeholders (HIV-positive mothers, EID providers, community members) (Table 1). Uptake of testing, by POC and SOC methods, will be quantified in terms of proportions of infants who are tested (have a documented specimen collection) in the birth and 6-week windows and the proportion of infants determined HIV-negative at birth who are presented again for retesting in the 6-week window.

**Table 1 Tab1:** Implementation and feasibility measures

Variable	Measure (for both POC and HIV DNA PCR tests, unless specified)	EID stage(s)
Acceptability/uptake	Mothers’ views of birth testing impact on infant, family	
	Provider recommendations/concerns on implementation	
	Community member attitudes and recommendations	
	Proportion (%) infants with specimen collected	Birth, 6 weeks^a^
	Median infant age at specimen collection	Birth, 6 weeks
	% Birth-tested infants returned for 6-week retest	Sequential
Infant testing outcomes	% Tests with results returned	Birth, 6 weeks
	% Tests with mother notified of results	Birth, 6 weeks
	Median turn-around time (TAT), specimen to test result availability	Birth, 6 weeks
	Median infant age at result availability	Birth, 6 weeks
	Median TAT, result availability to mother notification of results	Birth, 6 weeks
	Median overall TAT, specimen to mother notification of results	Birth, 6 weeks
	Median infant age at mother notification of results	Birth, 6 weeks
	Median infant age at ART initiation (if diagnosed HIV+)	Birth, 6 weeks
	Complete retention: % mothers notified of birth and 6-week results	Sequential
POC platform performance	Number failed POC tests, GeneXpert and Alere q	Pooled
	Number POC missed opportunities due to machine breakdown	Pooled
	Number POC missed opportunities due to machine error	Pooled
	Number POC missed opportunities due to cartridge stockout	Pooled
	Concordance of POC results (each platform) with HIV DNA PCR	Birth, 6 weeks
Provider feedback	Acceptability and feasibility of implementing birth and POC testing	
	Benefits and challenges of birth and POC testing for patients	
Costs of POC implementation	Acquisition of GeneXpert and Alere q machines	
	Acquisition of accessory equipment	
	Site-specific training, secure storage	
	Acquisition of test cartridges	
	Maintenance and repair of machines	

^a^Birth testing is denoted when specimen is collected at 0–2 weeks of age. “Six-week” testing is denoted when specimen is collected at 4 to < 24 weeks of age

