### Phase 2: intervention

#### Study design

We will pilot the implementation of POC and birth testing at four government hospitals over a 12 month period. The four study sites will be randomized, using a random number generator, to pilot one of the two POC systems (Xpert HIV-1 Qual for HIV RNA or Alere q HIV-1/2 Detect). SOC diagnostic testing (HIV DNA PCR test on DBS samples) will be conducted in parallel at all study sites, including the newly introduced birth testing time point. Patient flow in the pilot is diagrammed in Fig. 1.

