##### Birth testing

For all infants presenting for birth testing (within 2 weeks of age), the designated staff at each facility will collect two blood samples. A whole blood sample for POC testing (Xpert HIV-1 Qual or Alere q HIV-1/2 Detect) will be processed on-site by healthcare providers using test cartridges and POC machine. POC test results will be recorded in study logs and printout results from each of the POC machines will be attached to the infant’s clinical file (see *Data collection*, below). Mothers will be notified of the POC test result on the same day as testing or before infant’s hospital discharge (within 24 h). The second sample will follow the established SOC procedures for HIV DNA PCR testing: a dried blood spot (DBS) sample will be sent by courier to the hospital’s designated central laboratory for standard HIV DNA PCR. Results of HIV DNA PCR processed in the central laboratory will be recorded on paper forms and returned to the hospital by courier service. When the HIV DNA PCR result is received at the hospital, the mother will be called to return for result notification and counseling. If the infant has an HIV-positive test result (by either POC or PCR), the mother and infant will be linked to the Comprehensive Care Center (CCC) for same-day ART initiation. HIV-positive infants identified through this study will receive additional clinical monitoring (ART adherence, viral suppression, and immune system strength) through 24 months of age. HIV-negative infants will be scheduled to return to the hospital for six-week postnatal appointments and repeat HIV testing (HIV DNA PCR and POC).

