### Statistical analysis

This study is designed to gather preliminary outcome data to inform implementation guidance and pilot data for a subsequent larger study. We anticipate mean monthly enrollment per study site of approximately 15 eligible participants, yielding an estimated total enrollment of 720 mother-infant pairs by the end of the 12-month intervention phase. Reductions in study participation are expected to result from documented transfer to other facilities, loss to follow-up, miscarriage, and infant mortality prior to testing. Nonetheless, we anticipate ample power to describe and compare outcomes of birth testing and between POC and PCR testing strategies to estimate effect sizes and an intracluster correlation coefficient (ICC) to inform future sample size and power calculations.

Categorical variables will be presented as proportions, and continuous variables as means (SD) or medians (IQR) depending on the distribution of data. Quantitative measures compared across POC platforms or between POC and HIV DNA PCR testing methods will be analyzed using parametric and non-parametric (Exact or Wilcox and Rank-sum) tests.

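### PCR-side notification and age at ART initiation are observed after POC disclosure, so their POC-versus-PCR contrasts are not effects of one strategy against the other

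*Protocol article*

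**What the plan says.** All references are to the protocol article.

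- **Scope of the measures.** Table 1 heads its measures column "Measure (for both POC and HIV DNA PCR tests, unless specified". Under it stand percent of mothers notified, time from result to notification, overall time to notification, age at notification, and the row beginning "Median infant age at ART initiation (if diagnosed HIV". None of these is marked as applying to one test only.
- **Planned use.** The Statistical analysis section names tests for measures compared between POC and PCR, and expects enough power "to estimate effect sizes and an intracluster correlation coefficient (ICC) to inform future sample size and power calculations".
- **Design (Phase 2, Study design).** "SOC diagnostic testing (HIV DNA PCR test on DBS samples) will be conducted in parallel at all study sites". What is randomised is the hospital, "to pilot one of the two POC systems"; there is no PCR-only group.
- **Order of results (Birth testing).** "Mothers will be notified of the POC test result on the same day as testing", or before discharge, within 24 h. For PCR, "When the HIV DNA PCR result is received at the hospital, the mother will be called to return for result notification and counseling". Six-week testing follows the same sequence.
- **Start of treatment (Birth testing).** "If the infant has an HIV-positive test result (by either POC or PCR), the mother and infant will be linked" to same-day ART. The Discordant results section says the same where the two tests disagree.
- **Data collection.** Result and notification data are kept separately for each test, but only one ART initiation date is listed per infant.

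**The concern.** A comparison of two testing strategies needs outcomes that each strategy produced on its own. Here the two tests share an infant, a mother and a treatment decision. Steps up to the availability of each result run separately. After that the pathways merge: a mother recalled for the PCR result has normally already heard the POC result, and an infant positive on POC is normally on ART before PCR reports.

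At stake is the use of these numbers. They are meant to supply effect sizes for a later trial. An ART-age contrast close to zero would hide the gain that the article itself expects, since the section on ART adherence monitoring anticipates considerably earlier ART than under standard of care. A PCR notification rate taken as the standard-of-care rate would feed an uninterpretable figure into the next sample size.

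**Working it through.** **1. The plan's own figure.** 15 participants per site per month × 4 sites × 12 months = 720, which matches the stated enrolment and is not in dispute. No alpha, effect size or SD is given, so no power formula can be checked, and this point does not depend on one.

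**2. Which steps the other test can influence.**
- Result returned, specimen-to-result time, age at result availability: each test has its own specimen and processing route. The contrast is clean.
- POC notification: comes before the PCR result in the intended flow. A fair measure of POC.
- PCR notification (percent, time from result, overall time, age): normally observed after POC disclosure. Not PCR alone.
- Age at ART: one date per infant, set by whichever positive result acts first.

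**3. Age at ART: how often POC sets the date.** Among PCR-positive infants, the share whose ART is triggered by POC = (1 − f) × s, where s is POC sensitivity and f is the proportion with POC failed or unavailable.
- s = 0.933 to 0.987, from the Background section (laboratory evaluations with infant samples).
- f is not given; assumed 0 to 0.20.
- Low end: (1 − 0.20) × 0.933 = 0.746. High end: (1 − 0) × 0.987 = 0.987.
- So POC triggers ART in about 75–99% of PCR-positive infants, and PCR in about 1–25%.

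**4. Age at ART: what the contrast would show.**
- *Infants positive on both tests, counted in both columns:* same date twice, so a difference of exactly 0.
- *All POC-positive against all PCR-positive infants:* simulated with 200,000 infants in the birth window. Assumptions: age at specimen uniform over 0–14 days; ART half a day after the specimen if POC is positive; otherwise ART after an exponential PCR delay with median L.

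| Assumed L (days) | Difference in medians, parallel design (days) | Difference if PCR were used alone (days) |
|---|---|---|
| 14 | 0.1–1.8 | 13.9–14.0 |
| 28 | 0.1–2.0 | 27.5–27.8 |
| 42 | 0.1–2.1 | 41.5–41.8 |

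Ranges run over f = 0, 0.10 and 0.20 and s = 0.933 and 0.987. The delay L is an assumption; the article gives no PCR turnaround.

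- *Infants assigned to the triggering test:* the PCR group is the 1–25% whose POC test was mainly negative, failed or unavailable. The simulation treats POC failure as unrelated to PCR delay. The trial cannot rely on that: the Study status section reports an Alere q cartridge stock-out in the same initial months as a nurses' strike.

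**5. PCR notification.** No arithmetic is possible. The article gives no return rate with or without a known POC result. A mother reassured by a negative POC result might not come back. On the other hand, mothers are counselled to return for the birth PCR result and are called, and families of POC-positive infants are already linked to care. The effect could run either way.

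**The case against.** The strongest defence is that no sentence states a POC-versus-PCR contrast for ART age. The Table 1 header also covers rows where a value per test makes no sense, such as community attitudes. The ART row is split by testing window, the Infant testing outcomes section names the two tests in connection with turnaround times, and only one ART date is listed. One ART age per infant is thus a natural reading, and attribution to a test could be left to an analysis plan. The study is also a feasibility pilot that expects few HIV-positive infants.

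Part of this stands. It makes the point modest in consequence, and the authors may intend something close to the remedy. It does not remove the point. The header allows exceptions where specified and none is given here; the comparison of methods and its use for effect sizes are in the article. Later analysis wording cannot recover PCR-alone timing from a design without a PCR-only group.

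Four stronger readings are tempting and not supported:
- *That every mother hears POC first.* This is the intended flow, but the POC platform performance section plans to count failures, breakdowns and stockouts, in which PCR may come first or be the only result.
- *That the measures describe neither strategy.* POC notification, and ART age in POC-positive infants, are fair measures of POC. The contamination is mainly on the PCR side.
- *That the ART difference must be exactly zero.* This holds only for infants positive on both tests.
- *That the POC advantage in notification is overstated by some number of points.* Neither direction nor size follows from the documents.

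**Conclusion.** The point holds for the PCR side. As the table header and the Statistical analysis section are written, PCR values for percent notified, result-to-notification time, overall time to notification, age at notification and age at ART do not show what PCR alone would give, and their contrast with POC is not a strategy effect.

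It is clearest for ART age: either a near-zero contrast (about 0.1–2.1 days where PCR alone would differ by about 14–42 days) or a selected PCR group of about 1–25% of PCR-positive infants. That a shared date compresses the contrast follows from the design. The day figures rest on the assumed POC unavailability of 0–20%, the assumed PCR delays, and the article's sensitivity range. For PCR notification the conclusion is qualitative only. Separate reporting of notification dates by test is legitimate as description.

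**What to change.** 1. Limit POC-versus-PCR effect sizes to percent of results returned, specimen-to-result turnaround and age at result availability.
2. Report age at ART once per infant for the combined POC and PCR pathway, showing which result came first.
3. Report PCR notification measures descriptively, labelled as observed after POC disclosure where that applies, and state that they will not serve as a standard-of-care effect size.
4. If the within-infant gap between POC and PCR result availability is used to inform the gain in ART timing, state that it leaves out the recall time after the PCR result. It is an approximate figure that tends to be low, not a bound.

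This needs a Table 1 footnote and matching analysis wording. It uses result, notification and ART data already planned for collection, and changes neither testing nor treatment rules. The cost is fewer headline POC-versus-PCR contrasts; a true effect on PCR notification or ART timing would need a PCR-only comparator.

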In 2016, the WHO prequalified two point-of-care (POC) diagnostic tests for detection of HIV RNA in whole blood samples (Xpert HIV-1 Qual for GeneXpert instruments, manufactured by Cepheid AB; Alere q HIV-1/2 Detect manufactured by Abbott). Both tests are cartridge-based, real-time reverse transcription PCR qualitative assays performed with benchtop instruments that are suitable for operation in the clinic setting and do not require extensive technical training [22, 23]. The initial published evaluations of the Xpert HIV-1 Qual or Alere q HIV-1/2 tests performance were conducted by diagnosticians in the laboratory setting [22–25], showing good sensitivity (93.3–98.7%) and specificity (100%) with infant samples. By definition, the POC test systems provide optimum value in expediting EID if they are performed in the clinic setting, by clinical personnel. Field studies of both the Xpert HIV-1 Qual [26, 27] and Alere q HIV-1/2 [27–29] were performed in clinical care facilities, by medical caregivers. Sensitivity and specificity values were similar to those reported from the laboratory-based qualification studies, but in some instances the field studies produced higher rates of test error [26, 29]. Recent studies with large numbers of HIV-positive newborn infants show close concordance between SOC tests and both of these POC technologies [26, 27]. While analytic performance profiles of these POC technologies have been characterized in field studies, sustainable scale-up and optimal utility in Kenya and other resource-constrained countries requires robust implementation studies in diverse clinical settings. Currently, there is a lack of data to guide strategic implementation of the birth testing timepoint or the Xpert and Alere q POC testing platforms in Kenya. Here, we report the protocol for a pilot study to assess feasibility and preliminary impact of introducing birth testing as an addition to EID services, and to evaluate the two POC platforms in parallel with laboratory-based HIV DNA PCR.

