##### Data collection

Using Epi Info software (US Centers for Disease Control and Prevention), site coordinators will collect and maintain a comprehensive electronic record of each infant’s relevant clinical data including date of birth, location of birth, POC sample collection and processing dates, POC test results, POC result notification to mothers, dates of SOC sample collection and return of results to the hospital, results of HIV DNA PCR test, mother notification of HIV DNA PCR results, and date of initiation of HIV-positive infants on ART. To ensure complete and accurate clinical data entry, site coordinators will periodically cross-check Epi Info files with various clinical records including ANC registers, maternity records, HIV-exposed infant registers, mother and infant clinical files, and hard copies of laboratory diagnostic results. Data pertaining specifically to treatment of HIV-positive infants (including ART initiation, OI prophylaxis, and viral load and CD4 monitoring through 24 months) will be accessed from HIV exposed infant registers, CCC records, and infant clinical files.

Study-specific data collection logs will track enrollment across varying departments, reasons for enrollment refusal, use of the POC machines including dates and times of sample collection and processing and the personnel processing the test, POC machine errors and their effect on clinical care, adverse events that occur as a result of the study, communication between clinical or study staff and participants, and hospital or national-level events that may impact clinical care and study operations. These logs will help gauge implementation feasibility and provider experience. The principle investigator and IRB-certified research staff will have access to the final trial dataset, with no contractual hindrances.

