##### POC platform performance

Assessment of both the Xpert and Alere q HIV POC platforms will include evaluation of testing reliability (Table 1). Measures to be tracked include number of failed tests (and wasted cartridges), and number of missed opportunities to engage infants with POC testing due to documented machine breakdown, machine error, or cartridge stockout. The anticipated number of HIV-positive infants identified is too small to support robust sensitivity or specificity calculations, but we will track concordance between test results from each POC platform and the corresponding HIV DNA PCR results.

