POC testing also offers potential to improve EID system efficiency in low resource settings where there are multiple delays inherent in the laboratory-based HIV DNA PCR testing process. Sample testing in the clinic setting potentially facilitates mother notification of infant HIV status on the same day as test. To fully realize the POC technology’s potential at the true point of care, cadres of clinical providers must be trained to perform diagnostic procedures outside of traditional clinical duties. Therefore, in addition to traditional laboratory personnel, our pilot study includes training nurses to conduct POC testing within the Maternity and MCH settings. This pilot will solicit provider feedback regarding issues of patient flow, interdepartmental collaboration, and provider workload, while identifying potential barriers to this task-shifting approach during larger scale-up. Other performance measures reflecting the utility of POC platforms—such as user friendliness, equipment durability, test failure rate, costs of maintenance, and frequency of cartridge stockouts—will likely affect the consistency of testing operations and missed opportunities for diagnosis. This pilot study will track these variables and thus supply preliminary feasibility data to inform effective and sustainable POC interventions for larger future studies.

These novel data on implementation outcomes and clinical impact of birth HIV testing with POC and PCR testing strategies are timely given the movement toward more rigorous EID in low resource countries. Implementation and user satisfaction data from the two approved POC platforms, GeneXpert and Alere q, may also guide other groups considering investment in POC scale-up. By providing parameters to estimate effect size and intraclass correlation, these results will facilitate the design of properly powered pragmatic trials to evaluate the impact of birth and POC HIV testing in Kenya. These timely data may also facilitate wider adoption of 2016 EID guidelines issued by WHO and the government of Kenya to accelerate infant testing within the existing PCR infrastructure, while bridging the birth testing strategy to implementation of POC testing technologies.

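### Failed POC tests and machine-error misses are counted over birth and 6-week testing combined, so the planned failure measure does not show how reliable POC testing is at birth

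*Protocol article*

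**What the plan says.** Table 1 has a column for EID stage. Of its 17 quantitative testing and performance rows, 11 are marked for birth and 6 weeks separately, two are sequential by nature (return for retest, complete retention) and four are marked *Pooled*. The four are failed tests ("Number failed POC tests, GeneXpert and Alere q") and missed opportunities due to breakdown, machine error and stockout; the machine-error row reads "Number POC missed opportunities due to machine error Pooled". Concordance, in the same block, is split: "Concordance of POC results (each platform) with HIV DNA PCR Birth, 6 weeks".

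The text under POC platform performance also describes counts and names no stage: "Measures to be tracked include number of failed tests (and wasted cartridges), and number of missed opportunities to engage infants with POC testing".

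The Data collection section says that logs will record "use of the POC machines including dates and times of sample collection and processing and the personnel processing the test", along with machine errors. The infant's date of birth is in the electronic record. Platform is assigned by site, two hospitals each (Phase 2, Study design). The Statistical analysis section foresees comparisons across platforms.

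**The concern.** The pilot introduces a new testing time point, and the Objectives include tracking the reliability and performance of both POC platforms. Whether the POC test fails more often in newborns than in older infants is therefore a direct feasibility question. The Background gives a reason to look at field failures closely: "in some instances the field studies produced higher rates of test error".

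A count pooled over stage does not answer that question, and without a denominator it cannot be read as a rate. There is a second consequence. The share of tests done at birth need not be the same at every hospital. Women may be enrolled in pregnancy, at delivery or at a first postnatal visit, with infants eligible up to 24 weeks, so an infant enrolled after the birth window contributes only a 6-week test. Any such difference in stage mix would enter a crude platform comparison.

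**Working it through.** **The article's own figure.** 15 pairs per site per month × 4 sites × 12 months = 720, which reproduces the stated enrolment. This gives 720/2 = 360 pairs per platform and 720/4 = 180 per site. The article states no failure rate and no birth share; those below are assumptions.

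**Do the other stage-specific measures fill the gap?** Not fully.
- Concordance needs a POC result, so failed tests drop out of it.
- The results-returned measure, "Tests with results returned Birth, 6 weeks", covers POC as well as PCR. It would fall at a given stage when a POC test never yields a result. It does not give the cause, and, depending on how reruns are counted, it can hide a failure rescued by a rerun. Failed tests and wasted cartridges are named as measures in their own right.

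**What a pooled count hides.** Assume one test per infant, split evenly: 180 birth and 180 6-week tests on a platform.
- Failure 15% at birth and 5% at 6 weeks: 27 + 9 = 36 failures.
- Failure 10% at both stages: 18 + 18 = 36 failures.

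The planned row would show 36 in both cases.

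**Pooled rate for a birth share *s*:** *s* × f(birth) + (1 − *s*) × f(6 weeks).

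| Assumed failure, birth / 6 weeks | *s* = 30% | *s* = 50% | *s* = 70% |
|---|---|---|---|
| 15% / 5% | 8% | 10% | 12% |
| 10% / 5% | 6.5% | 7.5% | 8.5% |

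**Effect on the platform comparison.** Let both platforms have the same failure rate at each stage, but let one have 70% of its tests at birth and the other 30%.
- At 15% / 5% the crude rates are 12% and 8%, a spurious difference of 4 points. With 360 tests per platform the chance of a nominal two-sided p < 0.05 is about 43%.
- At 10% / 5% they are 8.5% and 6.5%, 2 points, with a chance of about 17%.
- With equal shares the difference is zero.

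These chances ignore clustering by site.

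**Is a split workable?** The 95% half-width is 1.96 × √(p(1 − p)/n).

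| n tests | p = 5% | p = 15% |
|---|---|---|
| 90 (one site, one stage) | 4.5 points | 7.4 points |
| 180 (one platform, one stage) | 3.2 points | 5.2 points |
| 360 (if every infant were tested at both stages) | 2.2 points | 3.7 points |

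Platform-by-stage estimates would be usable for a pilot; site-by-stage figures would be rough. Losses before testing, which the article expects, would widen all of these.

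**The case against.** The strongest reply is that nothing is lost for good. The logs hold collection and processing times and machine errors, and with the date of birth these place each test in its stage, so the split can be made at any time. The pilot is descriptive, the 6-week procedure repeats the birth procedure, and the article gives no evidence that failure depends on infant age. All of this is true. It limits the point to the measures as listed and does not remove it: *Pooled* is an explicit entry in a table that splits most other testing measures.

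It is also fair that breakdown and stockout are equipment and supply events. Pooling those two rows is reasonable.

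A reader might infer more: that failures are also pooled over nurses and laboratory staff, that the pilot therefore cannot show whether nurse-run testing is reliable, and that operator mix could pass for a platform difference. The documents do not support this.
- *Pooled* stands in the stage column and says nothing about operators.
- The Discussion says "our pilot study includes training nurses to conduct POC testing within the Maternity and MCH settings", but no objective compares operator types. A breakdown by cadre is detail that an analysis plan can supply, and the personnel running each test are logged.
- No operator mix by site and no failure rates are given. Assumed rates of 15% for nurses and 5% for laboratory staff, with nurse shares of 80% and 20%, would give 13% against 7%, but every one of those inputs is invented.
- With two sites per platform, comparing within cadre would still leave site differences tied to platform. Who runs the machine may also reflect how usable the platform is.

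**Conclusion.** The point holds for two rows of Table 1: failed POC tests and machine-error missed opportunities. As listed, they do not show whether POC testing is less reliable at 0–2 weeks than at 4 to under 24 weeks, and they leave a crude platform comparison open to differences in stage mix. On assumed failure of 15% at birth and 5% at 6 weeks, the pooled figure is 8% to 12%, and a 70% against 30% birth share creates a 4-point difference between identical platforms; at 10% and 5% it is 2 points. The true size is unknown, because neither failure rates nor stage shares are stated, and it is zero if failure does not vary with stage. No stated figure is wrong. This is an inexpensive improvement in reporting. It is not a flaw that makes the data unusable.

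**What to change.** In Table 1, change *Pooled* to birth and 6 weeks for failed POC tests and for missed opportunities due to machine error. Report each with its count and as a proportion of POC tests attempted, by platform and site, and compare platforms within stage. If a machine-error miss can occur before a test is attempted, say how it enters the denominator. Bring the text under POC platform performance into line. Leave the breakdown and stockout rows pooled.

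Optionally, add a descriptive table of failures by operator cadre from the logged personnel field, presented as description only. It would not correct the platform comparison for site differences.

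The cost is a few table rows from data already collected, with smaller cells and wider intervals: about 3 to 5 points either side per platform and stage at 180 tests, and 4.5 to 7.4 points per site and stage at 90.
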